# Study protocol of a 4- parallel arm, superiority, community based cluster randomized controlled trial comparing paper and e-platform based interventions to improve accuracy of recall of last menstrual period (LMP) dates in rural Bangladesh

**DOI:** 10.1186/s12889-018-6258-z

**Published:** 2018-12-10

**Keywords:** Gestational age, LMP, Recall, Preterm birth, Bangladesh, Mobile phone, M-health

## Abstract

**Background:**

Gestational age (GA) is a key determinant of newborn survival and long-term impairment. Accurate estimation of GA facilitates timely provision of essential interventions to improve maternal and newborn outcomes. Menstrual based dating, ultrasound based dating, and neonatal estimates are the primarily used methods for assessing GA; all of which have some strength and weaknesses that require critical consideration. Last menstrual period (LMP) is simple, low-cost self-reported information, recommended by the World Health Organization for estimating GA but has issues of recall mainly among poorer, less educated women and women with irregular menstruation, undiagnosed abortion, and spotting during early pregnancy. Several studies have noted that about 20–50% of women cannot accurately recall the date of LMP. The goal of this study is therefore to improve recall and reporting of LMP and by doing so increase the accuracy of LMP based GA assessment in a rural population of Bangladesh where antenatal care-seeking, availability and utilization of USG is low.

**Method:**

We propose to conduct a 4- parallel arm, superiority, community based cluster randomized controlled trial comparing three interventions to improve recall of GA with a no intervention arm. The interventions include (i) counselling and a paper based calendar (ii) counselling and a cell phone based SMS alert system (iii) counselling and smart-phone application. The trial is being conducted among 3360 adolescent girls and recently married women in Mirzapur sub-district of Bangladesh.

**Discussion:**

Enrolment of study participants continued from January 24, 2017 to March 29, 2017. Data collection and intervention implementation is ongoing and will end by February, 2019. Data analysis will measure efficacy of interventions in improving the recall of LMP date among enrolled participants. Results will be reported following CONSORT guideline.

The innovative conventional & e-platform based interventions, if successful, can provide substantial evidence to scale-up in a low resource setting where m-Health initiatives are proliferating with active support from all sectors in policy and implementation.

**Trial registration:**

ClinicalTrials.gov NCT02944747. The trial has been registered before starting enrolment on 24 October 2016.

**Electronic supplementary material:**

The online version of this article (10.1186/s12889-018-6258-z) contains supplementary material, which is available to authorized users.

## Background

Accurate estimation of gestational age (GA) is critical for providing optimal care during pregnancy, childbirth and postnatal period [1, 2]. It is essential for tracking fetal growth and appropriate administration of live saving interventions related to pre-term births such as antenatal corticosteroids therapy (ACS), Kangaroo Mother Care (KMC), tocolytics, and continuous positive airway pressure [1, 2]. The importance of accurate estimation of GA is paramount in Bangladesh as Prematurity/Low birth weight (LBW) accounts for 13% of all newborn deaths [3–5]. The national guideline of Bangladesh also recommends using ACS for women with threatened preterm deliveries between 24 and 34 weeks of GA and KMC for preterm/LBW babies [6–9].

Three methods of GA estimation are primarily used - menstrual based dating (LMP), ultrasonography (USG) and neonatal assessment, all of which have some strengths and weaknesses [10]. USG, based on biometric measurements of the fetus, is considered the gold standard when it is done before 20 weeks of gestation [11]. However, in low and middle income countries (LMIC) like Bangladesh, majority of the first antenatal care (ANC) contacts happen after 20 weeks of Gestation [3, 12]. Out of those who have an USG performed within 20 weeks, there are issues with validity and reliability of measurements due to the poor quality of equipment and inadequate skill of the health care providers [12, 13]. Moreover, USG is expensive, and the availability is limited in resource poor settings [12]. Neonatal assessments are based on standardized scoring systems of physical and neuromuscular maturity of the newborns. These are, however, less precise then USG, and also require skilled personnel [14]. LMP is a simple, low-cost method recommended by the World Health Organization [15]. However, several studies have shown that approximately 15–45% of pregnant women are unable to recall their LMP accurately [16–18]. The accuracy of LMP-recall is negatively influenced by digit preference, duration of the recall period, irregularity or individual variations in the length of the menstrual cycle, conception during the period of lactational amenorrhea, preconception amenorrhea and implantation bleeding [16–20]. The accuracy is further compromised by late presentation for the first antenatal care contact and minimal skills of the ANC providers in probing for an accurate LMP date. Reliance on LMP-recall as the only method for estimating GA may therefore result in overestimation of GA at the extremes of gestation, which is more common in women with no or low education and those living in poverty [16, 21]. Despite the limitations, studies conducted in Bangladesh and Guatemala has suggested LMP to be the preferred method for determining GA in low-resource settings [12, 22].

We therefore aim to determine the efficacy of three interventions targeted to improve LMP-recall among women in rural Bangladesh.

### Goals and objectives

The goal of this study is to improve the accuracy of LMP-recall based estimation of (GA). Through this trial we aim to determine the efficacy of paper based LMP dating calendar and e-platform based interventions (SMS based system and smart phone applications) in improving accuracy of LMP-recall among adolescent girls and recently married women in rural Bangladesh.

### Trial design

We propose to undertake a 4 - parallel arm, superiority, community based cluster randomized controlled trial comparing a no intervention arm with three intervention arms. The four arms are as follows:Arm 1: No intervention armArm 2: Counselling and a paper based calendarArm 3: Counselling and a mobile-phone based SMS alert systemArm 4: Counselling and smart-phone application

The trial was designed following SPIRIT guideline (Additional file 1). The design and randomization process has been illustrated in Fig. 1.

**Fig. 1 Fig1:**
[figure not shown]
Study design (created by authors)

## Methods

### Study setting

The study is being carried out in Mirzapur sub-district of Tangail district located at the northwest of Dhaka city, the capital of Bangladesh. Administratively, Mirzapur has 13 unions (the lowest administrative body with an average population of around 30,000), with 219 villages covering an area of 375 sq. km and a population of 3, 37, 496 (Fig. 2).

**Fig. 2 Fig2:**
[figure not shown]
Study area map (created by authors)

Since 2007, icddr,b has been running a demographic surveillance system (DSS) in 10 unions of Mirzapur covering 293,691 with a four monthly round. The trial will be implemented in the DSS area for ease of identification and enrolment of study participants.

### Participants

Adolescent girls (15–17 years of age) and recently married women (within past two and half years) with no or a single child residing in the selected villages has been enrolled to participate in the study. Table 1 shows the inclusion and exclusion criteria for enrolment.

**Table 1 Tab1:** Eligibility criteria

	Adolescents	Recently married women
Inclusion criteria	• Permanent resident of the study area (Adolescents who are usual residents of the households and living or intend to live in the area for 6 or more months)	• Permanent resident of the study area(recently married women who are usual residents of the households living or intend to live in the area for 6 or more months)
	• Aged between 15 and 17 years at the time of enrolment	• Aged < 45 years at the time of enrolment
	• Unmarried at the time of enrolment	• Married within the past two and half years with no or a single child
	• Parent or legal guardian is present at the time of recruitment and is willing to give assent for the adolescent’s participation	• Legal guardian is present at the time of recruitment and is willing to give assent for the participation of the recently married women aged < 18 years
Exclusion criteria	• Not applicable	• Pregnant or exclusively breastfeeding at the time of recruitment
	• Participant is mentally/physically challenged to provide consent	• Participant is mentally/physically challenged to provide consent

### Study arms

The study arms and interventions being tested in this study are described below:*Arm 1-no intervention arm*: In the no intervention arm, study participants follow their usual practices to recall LMP start and end dates; if any.*Arm 2- counselling and a paper based calendar*: This intervention entails counselling and documentation of menstrual bleeding dates on a paper based calendar. The topics of counselling include normal menstrual cycle length, abnormal bleeding, menstrual hygiene and importance of remembering and recording LMP dates. In addition, a free especially designed paper-based calendar is provided to the participant who prospectively records menstrual bleeding and spotting dates in each month. Likewise, if anybody forgets to record, she keeps a retrospective record of it in the subsequent month. Female counsellors from the study team conducted the individual education sessions.*Arm 3- counselling and a cell-phone based SMS alert system*: This intervention entails counselling and a cell-phone based SMS alert system. Counselling is similar to the calendar arm. Cell-phones are provided free of cost to the study participants who shares their first date of menstrual period every month to a designated number through an SMS. A automated-system is designed to record the dates from the SMSs. An SMS reminder is sent 3 days after the tentative start date of the cycle (as will be obtained from a LMP surveillance). If the user still does not input the start date, 2 other reminders are sent at an interval of 2 days. There is provision for sending unlimited LMP start dates in 1 month with restrictions to enter future dates. All the instructions are provided in Bangla. The charge of SMS for reporting LMP dates is free for the user.*Arm 4- counselling and smart-phone application*: Participants of this intervention arm received counselling and a free smart-phone with an application for recording menstruation dates and an inbuilt reminder system. Counselling is done on similar topics as the calendar arm. The smart phone based application is a password protected, colour-coded system for recording start date and end date of each menstrual cycle. The app is in Bangla (local language). Participants record start date and end date of their LMP each month in the application. There are provisions for entering dates for multiple cycles in a month and retrospective recording of dates (in case the user forgot to enter their previous cycles).

### Screening, consent & enrolment of study participants

The study participants (adolescent girls and recently married women) has been selected using DSS database. Participants selected from the DSS data base were approached by the field research staffs (surveillance workers) in a chronological way through household visits and enrolled in the study after getting written informed consent/ assent. Enrolment continued till the required sample size was achieved.

Two sets of consents/assents were taken from the study participants in the three intervention arms; one for participation in the intervention and the other for data collection. In the no intervention arm, consent/assent was obtained only for participation in data collection. Assent was taken from the legal guardians of all participants below 18 years of age. All the consent/assent forms are in Bangla for better understanding in local context. Details of the consent forms(purpose of the study, activities, risk, benefit, confidentiality, anonymity, future use of information, right not participate etc.) were read out and explained to study participants by the field research staffs before taking consent. Those who agreed to participate in the study signed two copies of consent/assent forms (thumb print were taken in case of illiterate participants); a copy of consent/assent was given to the study participant and the other one kept at icddr,b central office for record keeping.

### Delivering & monitoring the interventions

The roll out of interventions were arm specific. Female counsellors provided individual counselling to the enrolled study participants and handed over the specific interventions (paper-based calendars, mobile phones and smart phones) with adequate demonstration on how to record LMP-dates using the tools.

Adoption of interventions were reinforced by follow-up visits. For the first 2 months, each study participant received weekly household visit followed by biweekly visits in the subsequent 2 months. During the follow up visits, each participant were requested to record their LMP dates in the given tool and troubleshooting (device issues, balance & internet connectivity problems, forgot how to use the tools etc.) were done if needed. Participants are discontinued from the study in case of pregnancy (recently married women), marriage (adolescent girls), and permanent migration out of the study area, withdrawal of consent to participate etc.

Quality of intervention implementation are monitored by independent field research supervisors and investigators.

### Outcome measures

The primary outcome of this trial is the accuracy of LMP-recall dates. Accuracy of LMP-recall is defined as participants who will able to recall their start date of LMP within ±1 day of actual start date for their last menstrual cycle.

The secondary outcome of the trial is the certainty of LMP-recall dates. Participants will be asked to mention their level of certainty regarding their LMP-recall dates using the Likert scale ranging from 1 to 4 (highly certain, almost certain, somewhat certain, uncertain). Certainty will be defined if the participant are ‘highly certain’ regarding their recall for the last menstrual cycle.

Additionally we will also validate the LMP-dates recorded through the intervention tools with dates obtained from surveillance.

### Sample size

Sample size has been calculated to observe a minimum of 30% relative change in the primary outcome measure. We used STATA (comparison of two proportions in the presence of clustering effect) for sample size calculation. Assuming that in the rural context of Bangladesh approximately 55% of women can accurately recall LMP (at baseline without any intervention) [13], to measure a 30% relative change in recall as an effect of the intervention, we will require 252 participants from 28 clusters per arm (5% level of significance and 90% power). Accounting for 15% refusal and 20% loss to follow-up, the adjusted sample size was 420 adolescents and 420 recently married women per arm (Table 2).

**Table 2 Tab2:** Sample distribution

Number of samples					
	Arm1: Control arm	Arm2: Counselling & calendar (C + C)	Arm3: Counselling & SMS (C + S)	Arm4: Counselling & smart phone application	Total
Recently married women	420	420	420	420	1680
Adolescent girls	420	420	420	420	1680

### Participant timeline

The study will be conducted for 34 months. Enrolments continued till achievement of sample size. Interventions will be continued for 12 months. Detailed of the study timeline has been illustrated in Additional file 2.

### Study cluster formation, randomization & assignment of intervention

The trial administrator for this study was responsible for cluster formation and randomization of study clusters in the study arms using block randomization in stata.

At first, DSS data has been used to identify the required number of adolescent girls recently married women from the 10 unions after exclusion of high migration villages. One hundred twelve individual clusters were formed using GIS (geographic information system) technique with at least 15 adolescent girls and 15 recently married women per cluster. Buffer spaces between clusters (geographic spaces like river, roads, wet land, village boundary etc) were ensured during this exercise to reduce spill over effect.

All the field staffs (including managers and workers) & study participants were unaware of the intervention allocation during enrolment & baseline data collection. Recruitment of field research staffs were arm specific. Separate teams are responsible for data collection and intervention implementation for ensuring allocation concealment.

### Methods of data collection, management and analysis

Data for this study is being collected in the following ways:(i)
*LMP surveillance*

Actual LMP-dates of the enrolled study participants are being collected at two time points through 3-month long surveillances.. The baseline LMP surveillance was done before the start of implementation of interventions whilst the endline will be done before the end of implementation. A tab-based LMP surveillance tool (specially designed for this study), is used by field surveillance workers to collect this information through fortnightly rounds. No other information will be elicited from the participants during LMP-surveillance.(ii)
*LMP surveys*

A baseline survey was conducted among enrolled adolescents and recently married women in all arms before the start of the implementation of interventions. Face-to face interviews were done by trained data collectors using a structured questionnaire to elicit the required information. Participants were asked to recall their past 3 months LMP dates and their level of certainty regarding the LMP-recall dates. Information regarding demographic characteristics (age, sex, education, occupation), household’s socioeconomic profiles (housing status, assets, monthly income, ownership of mobile phone & accessibility to mobile phone), menstrual history were also collected. Recently married women were additionally asked regarding the use of contraceptive, pregnancy and birth outcomes. A similar survey will be conducted at endline.(iii)
*Data*
***e***
*xtraction from the intervention tools*

Data is extracted regularly from calendar records, SMS and smart-phones. The users of SMS arm sends their LMP dates via SMS whereas users of the smart-phone upload their data via the internet connected to the mobile-phone. For participants using the calendar, data collectors collect the information from the enrolled household every 2 months.

### Data management and analysis

#### Data management

Data quality will be ensured through rigorous training of the data collectors, refresher trainings and frequent spot checks by field supervisors. All the paper based data will be checked for completeness and will be entered into Microsoft access data base. An experienced data manager will be in charge of monitoring data quality. Any inconsistency will be resolved through rechecking the forms or by revisiting the households if possible. A real time online monitoring system (dash board) has been designed for quick and timely availability of information on intervention adherence, and data collection summary in intervention arms.

#### Data analysis

A participant flow diagram will be prepared following CONSORT 2010 guideline. Primary data analysis will be done on intention to treat basis. Analyses will be conducted at the individual level, and will be adjusted for cluster randomization.

For the primary outcome analysis, we will first examine the proportion of women accurately reporting LMP-dates at baseline and at endline. Differences in differences method will be used to ascertain the change. The analysis will be adjusted for confounders such as education, socio-economic status, and length of recall by bivariate analysis. Additionally, we will explore the change in mean and standard deviation of the difference between LMP-recall dates collected through LMP surveys and LMP-dates collected through LMP surveillance.

We will also validate the tools by comparing the distribution of LMP-dates recorded through the intervention tools with actual LMP-dates collected through LMP surveillance. Skewness and kurtosis tests of distribution of two LMP dates (recorded LMP and actual LMP) will be compared.

Stata® software version 10.1 (2008; Stata Corporation, College Station, TX, USA) will be used for all analyses.

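### The stated 90% power belongs to a clustered comparison of two proportions at one time point, not to the difference-in-differences named as primary; a baseline-adjusted endline model is at least as precise and needs no new data

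*Protocol article*

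**What the plan says.** The Sample size section of the protocol article names its method: "We used STATA (comparison of two proportions in the presence of clustering effect) for sample size calculation". It assumes that "approximately 55% of women can accurately recall LMP (at baseline without any intervention") and sizes the trial "to measure a 30% relative change in recall as an effect of the intervention". The result is that "we will require 252 participants from 28 clusters per arm (5% level of significance and 90% power"). After allowances of 15% for refusal and 20% for loss, the target becomes 420 adolescents and 420 recently married women per arm. The section mentions no baseline measurement, change score or correlation over time.

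The Data analysis section takes a different route for the primary outcome. Accurate reporting is tabulated at baseline and endline, and then "Differences in differences method will be used to ascertain the change". Analyses are at the individual level with adjustment for cluster randomisation. The section on methods of data collection confirms that recall surveys and LMP surveillance take place at baseline and at endline.

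**The concern.** The article states both the test used for sizing and the primary estimator, and they are different. A comparison at one time point carries the sampling error of the endline proportions only. DiD subtracts each arm's baseline proportion and so carries the baseline error as well. This pays off only when baseline and endline are strongly correlated.

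Clusters are randomised, so differencing is not needed to remove confounding. It amounts to fixing the coefficient on baseline at 1, whereas a regression on baseline estimates it. What is at stake is precision. If r is low, the trial could have less than its stated chance of detecting a 16.5-point effect, although the data for a more precise analysis are already being collected.

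**Working it through.** **Inputs from the article.** Control proportion 0.55; 30% relative increase, so 0.55 × 1.30 = 0.715 (difference 0.165); 5% level, taken as two-sided because sidedness is not stated; 90% power; 252 per arm in 28 clusters, so 9 per cluster.

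**Assumed, because not stated.** The ICC, and r, the baseline-to-endline correlation of cluster means.

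**1. Reproduce 252.** With mean proportion 0.6325:

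n = [1.96·√(2 × 0.6325 × 0.3675) + 1.2816·√(0.55 × 0.45 + 0.715 × 0.285)]² / 0.165² = 177.3, so 178 per arm.

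With ICC 0.05 the design effect is 1 + 8 × 0.05 = 1.4. Then 178 × 1.4 = 249.2, and 249.2/9 = 27.7, so 28 clusters and 28 × 9 = 252. The article's figure is recovered as a single-time-point clustered comparison. Other conventions would imply an ICC of 0.041 (continuity correction) or 0.092 (one-sided).

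**2. Sized comparison.** Let v0 = 0.55 × 0.45 = 0.2475 and v1 = 0.715 × 0.285 = 0.2038. Effective n per arm is 252/1.4 = 180.

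Variance = (v0 + v1)/180 = 0.4513/180 = 0.002507; SE 0.0501; power = Φ(0.165/0.0501 − 1.96) = 90.9%.

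**3. DiD.** Take baseline 0.55 in both arms and endline 0.55 against 0.715:

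Variance = [3·v0 + v1 − 2r(v0 + √(v0·v1))]/180 = (0.9463 − 0.9442r)/180.

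This equals the sized comparison when r = (0.9463 − 0.4513)/0.9442 = 0.52. DiD reaches 90% power at r of about 0.51.

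**4. Baseline-adjusted endline.** Variance = 0.4513 × (1 − r²)/180. This never exceeds the variance in step 2. With equal variances the ratio of DiD to baseline-adjusted variance is 2(1 − r)/(1 − r²) = 2/(1 + r), which is above 1 for every r below 1.

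Power at 252 per arm, ICC 0.05:

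| r | DiD variance ÷ sized variance | DiD power | Baseline-adjusted power |
|---|---|---|---|
| 0 | 2.10 | 62.4% | 90.9% |
| 0.2 | 1.68 | 72.0% | 92.0% |
| 0.3 | 1.47 | 77.6% | 93.2% |
| 0.4 | 1.26 | 83.5% | 94.9% |
| 0.5 | 1.05 | 89.5% | 96.7% |
| 0.6 | 0.84 | 94.9% | 98.5% |

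**5. Other analysed sizes.** The same formulas with ICC 0.05:

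- Both allowances applied to 420: 420 × 0.85 × 0.80 = 286 per stratum, 10.2 per cluster, design effect 1.46.
- 20% loss only: 420 × 0.80 = 336 per stratum, 12 per cluster, design effect 1.55.
- Strata pooled after 20% loss: 672 per arm, 24 per cluster, design effect 2.15.

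| r | DiD at 286 | DiD at 336 | DiD pooled, 672 |
|---|---|---|---|
| 0.2 | 75.5% | 79.7% | 91.8% |
| 0.3 | 80.9% | 84.7% | 94.8% |
| 0.4 | 86.4% | 89.6% | 97.2% |

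**6. Where r might lie.** Suppose the cluster effects correlate 0.5–0.8 over time and individual responses 0.1–0.3. With 9 per cluster and ICC 0.05, the cluster share of the variance of a cluster mean is 0.05/(0.05 + 0.95/9) = 0.32. Then r runs from 0.32 × 0.5 + 0.68 × 0.1 = 0.23 to 0.32 × 0.8 + 0.68 × 0.3 = 0.46. Over that range DiD power is about 74–87% at 252, 78–91% at 286, 82–94% at 336 (r rises slightly with cluster size), and 95% or more if pooled.

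**The case against.** The strongest reply is that nothing in the article shows the trial to be underpowered. r and the ICC are not given, and if village-level recall is stable over time, r could exceed 0.5, where DiD beats the sized comparison. The 252 is a minimum. The target is 420 per stratum, enrolment ran until the target was met, and refusal precedes enrolment, so 336 per stratum is a fair expectation. The article does not say that the strata will be analysed separately, and pooling would lift DiD above 90% for r of 0.2 or more. All of this stands, and it limits how large a loss can be claimed.

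DiD is also a legitimate estimator in a randomised trial with baseline data in every arm. A reader might infer that it is biased, or that it mishandles chance baseline imbalance in a way that invalidates the result. The documents do not support that: any over-correction is conditional on the imbalance observed, and the estimator is unbiased over randomisations. Nor did the sizing ignore clustering, which it expressly allowed for.

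Finally, the exact model form is usual material for an analysis plan that is not at hand. That covers details such as mixed model or GEE. It does not cover the mismatch, because the article itself states both the sizing test and the primary method.

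**Conclusion.** The point holds as a matter of precision and of correct reporting. The 90% figure describes a clustered comparison at one time point and is not shown to apply to the primary analysis. Whether DiD falls short of 90% depends on r and on the analysed N, neither of which the article settles. At 252 per arm it falls short for r below about 0.5; at 336 per stratum, for r below about 0.4; with pooled strata, only for r below about 0.2. Low-to-moderate r is plausible for a binary outcome on one cycle, measured roughly 11 to 17 months apart (baseline April to October 2017, endline from mid-September 2018), but that is a judgement and not a figure in the article.

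A reader might infer that the trial necessarily runs a noisier test than the one it sized. That is not supported, since the ordering reverses above r of about 0.52.

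One conclusion does not depend on r: baseline adjustment is at least as precise as the sized comparison, and more precise than DiD at every r below 1. The power figures rest on a normal approximation, an inferred ICC of 0.05, the same ICC in both strata when pooled, and no gain from the other planned covariates.

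**What to change.** Make the primary analysis a cluster-adjusted model (mixed model or GEE) of endline accuracy within ±1 day on arm, adjusted for the participant's own baseline accuracy and the cluster's baseline proportion. Keep DiD as a sensitivity analysis. Restate the power for the model actually used, giving the assumed ICC, the assumed r, the analysed N and whether the two strata are pooled. If DiD remains primary, give its power and the r on which it depends. Record the change before endline data are analysed.

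The cost is small: a change of analysis wording and no new data. Participants without a baseline value need a simple stated rule, for example a missing indicator.

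### The tool validation never counts a cycle without a tool entry as a failure, so it cannot tell a tool that captures nearly all cycles from one that misses many

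*Protocol article*

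**What the plan says.** Outcome measures adds a validation exercise to the primary and secondary outcomes: "Additionally we will also validate the LMP-dates recorded through the intervention tools with dates obtained from surveillance". Data analysis gives the method as "comparing the distribution of LMP-dates recorded through the intervention tools with actual LMP-dates collected through LMP surveillance" and names the statistics: "Skewness and kurtosis tests of distribution of two LMP dates (recorded LMP and actual LMP) will be compared".

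The reference dates come from surveillance: "Actual LMP-dates of the enrolled study participants are being collected at two time points through 3-month long surveillances". Only the endline round falls while the tools are in use, because the baseline round preceded implementation.

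The article expects some cycles not to be entered on time:

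- Calendar (Study arms): "if anybody forgets to record, she keeps a retrospective record of it in the subsequent month".
- SMS (Study arms): "If the user still does not input the start date, 2 other reminders are sent at an interval of 2 days".
- App (Study arms): forgotten cycles can be entered later.
- All tools (Delivering & monitoring the interventions): "troubleshooting (device issues, balance & internet connectivity problems, forgot how to use the tools etc.) were done if needed".

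Data management describes a dashboard that shows adherence. It serves monitoring and is not linked to the validation.

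**The concern.** The thing to be declared valid is the tool, but the tool's side of the comparison consists only of dates that somebody entered. A tool meant to supply an LMP date fails when it holds none. The stated method has no place where that failure appears.

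The route by which a date reaches the database also differs by arm: SMS entries are prompted by reminders, app data need an internet upload, and calendar data are collected by hand every 2 months. Capture may therefore differ between tools, and the validation would not show it. At stake is what the trial reports about each tool as a source of dates. Whether the interventions improve recall is a separate question.

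**Working it through.** The plan states no figure for the validation, so there is none to reproduce. The check asks whether the stated statistics respond to capture.

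**1. Logic.** Let N be the number of surveillance-confirmed cycles, c the share with a tool entry, and a the share of entries within ±1 day of the surveillance date. Skewness and kurtosis are standardised third and fourth moments. If entries are missing at random, their expected values are essentially the same whether N or cN dates are used. If p-values of skewness and kurtosis tests are compared instead, these depend on the number of dates, but a difference in p-value is not a measure of capture.

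**2. Inputs.**
- Women per arm (Sample size section): 420 + 420 = 840. Applying the article's 15% refusal and 20% loss gives 840 × 0.85 × 0.80 = 571.
- Cycles per woman in a 3-month round: 3 (assumed), so N = 571 × 3 = 1,713.
- Cycle length: mean 28 days, SD 3 (assumed).
- Entry error: 90% exact, 10% one day off (assumed), so a = 100%.
- Capture c: not given; range 10% to 100%, missing at random (assumed).

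**3. Simulation, 400 runs per setting.** Means over runs; kurtosis is excess kurtosis. The last two columns are a Kolmogorov–Smirnov (KS) test, added as a generic comparison of distributions, and the all-cycle measure c × a.

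| c | Skewness, actual / recorded | Kurtosis, actual / recorded | KS p < 0.05 | c × a |
|---|---|---|---|---|
| 100% | 0.034 / 0.034 | −1.164 / −1.163 | 0% | 100% |
| 90% | 0.034 / 0.033 | −1.165 / −1.164 | 0% | 90% |
| 50% | 0.035 / 0.032 | −1.164 / −1.162 | 0% | 50% |
| 20% | 0.034 / 0.035 | −1.163 / −1.157 | 0.2% | 20% |
| 10% | 0.034 / 0.030 | −1.163 / −1.139 | 1.8% | 10% |

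The run-to-run SD of recorded skewness grows from 0.007 at full capture to 0.108 at 10%. A single trial would therefore be noisier at low capture, but without a shift that points to missed cycles.

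**4. A better statistic alone does not cure it.** A paired ±1-day measure on recorded dates would be 100% in every row, because a pair exists only where an entry exists. With a less perfect tool (assumed c = 50%, a = 95%), agreement among recorded dates is 95%, while the share of all cycles with a correct date is 0.50 × 0.95 = 47.5%. At c = 40% and 80% it is 0.40 × 0.95 = 38% and 0.80 × 0.95 = 76%.

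**The case against.** The strongest reply is that the article is silent rather than wrong. Linkage, denominators and missing entries in an additional analysis can be left to the full protocol or SAP, and accuracy of entries is a legitimate question apart from completeness. Part of this stands. But the article does fix a method and its statistics, and following them as written gives no information on capture.

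Four stronger readings are tempting, and the article does not support them:

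- *Unrecorded cycles are dropped from the comparison altogether.* Pairing is not stated. Such cycles may remain in the surveillance distribution. They are still not counted as failures.
- *An inflated percentage valid will be reported.* No such percentage is planned for the tools; the ±1-day definition belongs to participants' recall. The percentages in step 4 only illustrate the principle.
- *The ranking of calendar, SMS and app could reverse.* No ranking on validation is planned; the design compares each intervention with no intervention.
- *A rarely used tool gains efficacy credit.* The primary analysis is by intention to treat on recall asked by survey, so a woman who ignores her tool still counts in her arm.

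It is also fair that reminders, visits and retrospective entry are safeguards. They show that missed entries are foreseen, not how many remain. The dashboard makes a capture rate obtainable but is not part of the validation. Finally, the simulation assumes random missingness. Selective missingness could change the shape, but a changed shape would still not measure capture.

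**Conclusion.** The point holds as a limited one. The validation as described cannot separate a tool that captures nearly all cycles from one that misses many: between 100% and 10% capture, mean recorded skewness moved only from 0.034 to 0.030 and mean kurtosis only from −1.163 to −1.139. This rests on the assumed cycle lengths, entry errors and random missingness. How far any real tool falls short is unknown, since capture rates are not given and retrospective entry may fill some gaps. The change is worth making because the written method can mislead about the tools. It does not touch the primary outcome.

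**What to change.** Replace the comparison of distributions, or supplement it, with a cycle-level validation over the endline surveillance window:

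1. Denominator: every surveillance-confirmed cycle start in that window, for participants of the arm still in follow-up.
2. Match tool and surveillance dates by woman and cycle, using a rule fixed in advance that also says how retrospective entries are treated. Wait for the last two-monthly calendar collection before closing the calendar data.
3. Classify each cycle as tool date within ±1 day, tool date further off, or no entry.
4. Report by arm, with cluster-adjusted intervals: (a) the share of cycles with a tool entry; (b) agreement within ±1 day among recorded cycles; (c) the share of all cycles with a tool date within ±1 day, with no entry counted as not captured.
5. Count tool entries with no matching surveillance cycle separately.

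The cost is revised analysis wording and one linkage step, on surveillance and tool data the trial already plans to collect. The downside is that the reported validity of each tool will be lower wherever entries are missing.
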